### Recruitment

The youth coach assesses the SSM-D during the first intake at the social welfare agency. If a young adult meets the *multi-problem* definition, a computer notification will alert the youth coach that the young adult should be referred to the researcher. When referred, the researcher will provide information about the trial to the young adult immediately after the intake. The baseline measurement will be conducted during the statutory effort period. Prior to start of T0, written informed consent will be obtained. As mentioned previously, when the participant returns to the social welfare agency for the second part of the intake after 4 to 6 weeks and meets the criteria of the social welfare agency, he will be referred to the allocated treatment condition (see Fig. 1). If a participant has acute psychological problems (e.g., suicidality), the statutory effort period can be skipped to arrange psychological help immediately. We aim to carry out the T0 and randomization before the actual treatment starts.

To gain full cooperation of the social welfare agency we will inform and involve the staff as much as possible, since other researchers have pointed out that it could take much effort to obtain the cooperation of referrers regarding the randomization [45, 79, 80]. Referrers may have their own ideas about the successfulness of participating interventions and might be hesitant to distance themselves from their professional judgment [79]. Therefore, we will inform and involve the staff as much as possible by notifications, presentations, manuals, newsletters, staff meetings, celebrations of milestones, and daily presence at the social welfare agency. In addition, we have set up a discussion group, consisting of staff members with different job functions, to exchange the experiences regarding the study implementation.

The recruitment at the social welfare office will be carried out by PhD researchers and research assistants. Research assistants will assist with the assessments. The whole research team will be trained extensively before they conduct interviews.

### Conditions

#### Experimental condition

Young adults in the experimental condition will participate in the multimodal day treatment program DNK [81]. The target group of DNK consists of young adult males aged between 18 and 27 years with problems on multiple life domains such as mental health problems, debts, delinquency, substance use, unemployment and a lack of daily structure. The mission of DNK is to reintegrate these young adults into society by increasing the self-sufficiency of their participants and reducing their delinquent behavior. DNK aims to increase the quality of life of these young adults, to improve their psychological functioning, to modify their distorted thinking and to decrease their substance use. Finally, DNK aims to help participants to find work, school or – if necessary – additional mental health care at the end of the program.

DNK offers an integrative, multimodal approach which is provided by a multidisciplinary team consisting of social workers, behavioral trainers, teachers, a psychologist and a psychiatric nurse. DNK has an open setting without security in which a prosocial attitude, and compliance with societal norms and values are constantly promoted by the staff. DNK offers a diverse, phased day program with free breakfast and lunch included. The intervention comprises educational and work services, mental health care, social work and coaching. The intervention has an average duration of 6 months, but is adapted to the individual needs of participants. In the first phase of the program, there are a few key points of focus: creating an adequate day-night rhythm, getting the participants accustomed to a daily structure, creating motivation for change and supporting practical needs (e.g., housing and debts). Within this initial phase, the participant is screened for psychological problems and addiction. When the program commences, coaching and education in the Dutch language, mathematics, social and health education, sports and art also start immediately. These classes are continued and extended within the second phase of the program by specific (motivational and cognitive-behavioral) trainings and by improving learning and general worker skills, for which participants can obtain various certificates. In the third and last phase of the program, participants are prepared for enrolling (back) into school or work; for example, via a short internship, training in job application, or support in choosing an appropriate education. This phase is completely tailored to the individual needs with regard to content and intensity, whereas the first and second phases of the program usually have an intensity of 4 days a week with the possibility of individual support at the fifth day.

Two main additions to the aforementioned program are possible. First, DNK participants in need for psychological and/or psychiatric care can receive extensive diagnostic research and treatment simultaneously with, or before, the start of the DNK program in collaboration with an institution for mental health care and addiction. A psychologist and psychiatric nurse are physically present at DNK to provide accessible support. Secondly, DNK participants with very severe problems can receive outreaching assistance in which DNK, for example, visits the participants at their home [81].

#### Control condition

The control condition consists of other available interventions in Rotterdam which can all be distinguished from the multimodal approach of DNK. These interventions usually focus on one or some, but not all, of the following components: mental health care, practical support, day activities, education or coaching. When participants are randomized to the control group, the youth coach decides – as is the case in normal practice – to which intervention a participant will be referred. It is expected that most participants in the control condition will be referred to either Challenge Sports (CS; a day program focused on education and coaching by professional athletes as role models) or Aan De Slag Met Zorg (ADSMZ; a collaboration of the social welfare agency with various mental health care institutions). Both programs partly include the same population according to the SSM profile of DNK participants. Referral to other, smaller interventions is also possible.

We only include participants who are referred to the interventions via the social welfare agency. Notably, some interventions have other referral paths as well. The young adults referred from other agencies are not approached for participation in this RCT.

### Instruments

Table 1 shows an overview of concepts, instruments and sources of information as well as assessment points. The main follow-up measurements are at 8 (T2) and 14 (T3) months after baseline (T0). The period between intake at the social welfare agency and start of the intervention is about 2 months. We expect to monitor the development of the participants for approximately 1 year after start at an intervention. To gain more insight into the specific changes during the interventions, follow-up measurement at 2 months after start of treatment (T1) will be conducted. This also allows us to compare interventions irrespective of differences in duration before start. To control for different timeframes before the start of the intervention, the SSM-D will also be completed by telephone (or face-to-face if possible) at the start of the intervention. In case of dropout, T1 will take place at 4 months after T0, which is estimated to be approximately at the same time as the adherent group. Questionnaires regarding the intervention will be filled out at T1 and, if the participant is still in the program, at T2. The researchers will give assistance to the participants during the assessments by reading out the questionnaires.

**Table 1 Tab1:** Concepts, instruments and sources at the different assessment points

Outcomes	Concept	Instrument	Assessment point						Source			
			T0	T1	T2	T3	T*s*	T*e*	Y	P	F	R
Primary	Recidivism	Judicial record									x	
		SRD	x		x	x			x			
	Self-sufficiency	SSM-D	x	x	x	x	x					x
Secondary	Quality of life	MANSA	x	x	x	x			x			
	School/work	Registration system			x	x					x	
	Psychopathology	ASR	x		x	x			x			
	Cognitive distortions	HIT	x	x	x	x			x			
	Substance use	MATE	x		x	x			x			
Moderators (participant characteristics)	Demographic factors	Demographic questionnaire	x	x	x	x			x			
	Intelligence	WAIS-III SF		x					x			
		SCIL	x						x			
	Criminal history	SRD	x						x			
		Judicial record									x	
	Motivation	VMB^a^		x	x				x			
Moderators (treatment characteristics)	Group climate	GCI^a^		x	x				x			
	Therapeutic alliance	WAV^a^		x	x			x	x	x^b^		
	General program characteristics	Registration systems (e.g., RMW)									x	
Program integrity DNK	Program integrity	Self-developed questionnaire						x	x	x		
	Characteristics and experiences staff	Self-developed questionnaire^c^								x		
Cost-effectiveness	Costs	Cost questionnaire				x			x			

*T0* baseline measurement; *T1* follow-up at 2 months after start intervention (adherence) or 4 months after T0 (nonadherence); *T2* follow-up at 8 months after T0; *T3* follow-up at 14 months after T0; *Ts* measurement of SSM-D at start intervention; *Te* measurement of program integrity and WAV at the end of intervention (only in the experimental group). *Y* young adult, *P* professional, *F* files/register information, *R* researcher. *ASR* Adult Self-report, *DNK* De Nieuwe Kans, *HIT* How I Think questionnaire, *GCI* Group Climate Inventory, *MANSA* Manchester Short Assessment of Quality of Life, *MATE* Measurements in the Addictions for Triage and Evaluation, *SCIL* Screener voor intelligentie en licht verstandelijke beperking, *SRD* Self-report Delinquency Scale, *SSM-D* Self-Sufficiency Matrix – Dutch version, *VMB* Motivation for Treatment Questionnaire–Short Form, *WAIS-III SF* Wechsler Adult Intelligence Scale - Short Form (third version), *WAV* Werk Alliantie Vragenlijst

^a^These questionnaires are only filled out when the respondent follows the program or has just finished it. ^b^DNK professionals only fill out the WAV at T*e.*
^c^This questionnaire will be filled in twice a year for a total of 4 times

#### Primary outcomes

The primary outcomes are *recidivism* and *self-sufficiency*. Recidivism will be scored from official judicial records. These records provide information about the type, frequency and severity of offenses as well as time to offenses [82]. The observation period will begin at T0. We will gather data on official arrests from 6 months before baseline as well to obtain insight into the history of registered offenses. Additionally, self-reported delinquency will be measured at T0, T2 and T3 by 29 items of the *Self-report Delinquency Scale* (SRD) [83]. This questionnaire consists of a total delinquency score that can also be divided into five subscale scores: public order offenses, property crimes, violent crimes, drug-related crimes and owning illegal weapons. Participants are asked if they have committed specific offenses (“yes” or “no”) as well as how often they have done so in the last 6 months.

Self-sufficiency will be measured with the Dutch version of the Self-Sufficiency Matrix (SSM-D), based on the American version of the SSM [84] and adapted to, and validated for, the Dutch population [39, 85, 86]. Self-sufficiency is being able to create an acceptable level of functioning on the important domains of life [87]. The SSM-D consists of 11 life domains: income, daily activity, housing, mental health, physical health, addiction, general life skills, social network, community involvement and justice. A trained researcher allocates, based on the information of the participant, a score between 1 (acute problems) and 5 (completely self-sufficient) to each SSM domain indicating the degree of self-sufficiency. The SSM is administered at T0, T1, T2, T3 and start of intervention. A compounded, overall self-sufficiency score will be developed for the primary analysis in collaboration with the developers of the SSM-D (Public Health Service in Amsterdam).

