Given the evidence for multimodal interventions in general [27, 44] and for specific components of DNK, we expect positive effects of DNK. In the present study a parallel-group randomized controlled trial (RCT) will be conducted. The first aim is to examine the effectiveness of DNK compared to care as usual (CAU) in terms of (1) reducing recidivism and (2) improving self-sufficiency as primary outcomes and in terms of (3) improving quality of life, (4) attending school/work, (5) improving psychological functioning, (6) reducing cognitive distortions and (7) reducing substance use as secondary outcomes. The secondary outcome measures are important objectives of DNK and (indirect) outcomes of the intervention. The second aim of this study is to obtain insight into the development of the primary and secondary treatment outcomes over time and to explore potential moderating effects. Potential moderators are participant and program characteristics, including program integrity. The third aim is to calculate the societal costs by conducting a cost-effectiveness analysis.

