Multi-problem young adults aged between 18 and 27 years will be recruited after their first interview at the social welfare agency in Rotterdam. After informed consent is obtained, baseline measurement (T0) will take place. After T0, the random assignment (with a ratio between DNK and CAU of 1:1) will be carried out by the first author. The random allocation is determined via an online computer program for randomization (www.random.org). Subsequently, the randomization numbers will be kept in sealed envelopes at the social welfare agency. During the baseline measurement the participant, researcher and youth coach will still be blind to the treatment condition. The first author will inform the youth coach about the outcome of the randomization. Only at the second interview will the young adult be informed by the youth coach about the assignment to the treatment or control condition. During the phase between the first and second interviews, the so-called statutory effort period, no intervention takes place. Only the participants who return for a second interview can be referred to an intervention. Therefore, participants who do not return within the run-in period will be excluded from the analyses. In this way, the statutory effort period is considered as a run-in period [74, 75] to deal with the estimated dropout rate of approximately 40% (p. 9) during this period [71]. Although some researchers have pointed out that a run-in period may influence the generalizability of the results [74, 76], it will improve the internal validity – the primary condition for valid outcomes – of our study [77]. Of the subjects who will be excluded during the run-in period, data will be collected at the follow-up measurements to compare the outcomes of the included and excluded groups and to incorporate this in generalizations from the study [74]. Figure 1 shows the flowchart of this study and Fig. 2 shows the SPIRIT schedule of enrollment, interventions and assessments.

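### The SSM-D, a primary outcome, is a researcher's judgement; blinding is stated for baseline only, and follow-up tasks give raters ways to learn the arm

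*Protocol article*

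**What the plan says.** Under Primary outcomes, the protocol article describes the SSM-D rating: "A trained researcher allocates, based on the information of the participant, a score between 1 (acute problems) and 5 (completely self-sufficient". Table 1 gives the researcher as the only source for this instrument. On timing: "The SSM is administered at T0, T1, T2, T3 and start of intervention". Statistical analysis takes T3 as the time point for the main effect and compares the arms on continuous outcomes with an independent-samples t test.

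The article's one statement on blinding is in Design: "During the baseline measurement the participant, researcher and youth coach will still be blind to the treatment condition". The same section says of allocation that "the random assignment (with a ratio between DNK and CAU of 1:1) will be carried out by the first author". The participant hears later: "Only at the second interview will the young adult be informed by the youth coach about the assignment". That interview comes before every follow-up rating.

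Instruments sets out the follow-up work. At programme entry, "the SSM-D will also be completed by telephone (or face-to-face if possible) at the start of the intervention". For the forms on climate, alliance and motivation, "Questionnaires regarding the intervention will be filled out at T1 and, if the participant is still in the program, at T2". Researchers read the questionnaires aloud. Participants still in a programme are also asked about their attendance and experiences at T1 and T2 (treatment-characteristics moderators). At T3 a cost questionnaire asks about services used in the preceding three months (Cost-effectiveness). In Background the authors write that "we expect positive effects of DNK".

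**The concern.** The SSM-D turns a conversation into a 1-to-5 score on domains such as social network, community involvement and general life skills. Such scoring leaves room for discretion. A rater who knows the programme and hopes that it works can score a borderline answer upwards without meaning to.

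The article limits blinding to baseline, and the word *still* in that sentence marks a state that ends. From then on the interviewing team has several occasions to hear which programme a man attends, and every man who returned for the second interview can tell them.

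The planned analyses cannot repair this. Intention-to-treat, multiple imputation, the t test and the mixed models all use the same ratings, so a difference between arms in how men are scored looks the same as a treatment effect. The possible result is a positive SSM-D finding beside a null finding on judicial records, with no way to tell whether the difference is real.

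**Working it through.** **1. Which follow-up tasks can reveal the arm, and how strongly**

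- *SSM-D at programme start, and T1 timed from that start.* The team must track programme entry. The date alone does not reveal the arm, because CAU men are referred to programmes too. A contact made at the moment of entry easily does.
- *Programme questionnaires read out at T1 and T2.* This is the strongest route: the rater hears answers about one particular programme. It applies only to men who are in a programme or have just finished it, and not at T3.
- *Cost questionnaire at T3.* It covers months 14 − 3 = 11 to 14. Programmes start about 2 months after intake and DNK lasts 6 months on average, so a typical DNK man finishes at about month 2 + 6 = 8. The window therefore often misses DNK; it catches a man who starts at month 2 and stays 9 months or longer.
- *End-of-programme (Te) forms.* They exist only in the DNK arm, but the participant and his coach complete them, so they are weak evidence about raters.

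The T3 rater is therefore most likely to know the arm by having done the same man's earlier visits or by being told. The article does not say whether one person rates a man throughout.

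**2. The plan's own sample size**

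The power analysis gives alpha .05, power .80, a small to medium effect and about 100 per arm, with no number for the effect and no sidedness. Assuming a two-sided test and d = 0.40:

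n = 2(1.960 + 0.842)² / 0.40² = 15.70 / 0.16 = 98.1, so 99 per arm.

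The exact t-test power at 100 per arm is .804. The stated 100 is reproduced, with d = 0.40 as a back-solved value. With the cited 34% dropout, 150 × 0.66 = 99.

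**3. Sensitivity to an assumed rating shift**

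Suppose there is no true effect and unmasked rating moves the DNK−CAU difference by b SD. The document gives no value of b, so the values below are assumptions. The chance of p < .05 two-sided is the power of the t test at d = b, with df = 2n − 2 and noncentrality b√(n/2).

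| b (SD) | Noncentrality, n = 100 | P(significant) | Noncentrality, n = 150 | P(significant) |
|---|---|---|---|---|
| 0 | 0 | 5% | 0 | 5% |
| 0.10 | 0.71 | 10.8% | 0.87 | 13.9% |
| 0.15 | 1.06 | 18.4% | 1.30 | 25.4% |
| 0.20 | 1.41 | 29.1% | 1.73 | 40.8% |

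A shift of 0.20 SD is half of the back-solved 0.40. If only half of the ratings were unmasked, a 0.20 SD shift among those would average 0.5 × 0.20 = 0.10 SD.

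**4. How many ratings can still be changed**

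Trial status gives first randomisation on 24 July 2014, end of recruitment on 17 November 2016, and data collection to January 2018. Men who entered by 17 September 2015 had reached month 14 when recruitment closed. That is 420 of 847 recruitment days, or about 50% if accrual was even (an assumption). About half of the T3 ratings were then still to come, and fewer by any later start.

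**The case against.** A reader might infer that the T3 ratings come from people who know the arm, and that the bias must favour DNK. The article supports neither as fact. It says that the first author allocates and informs the youth coach; it does not say that this person rates participants or tells the interviewers. T2 and T3 are timed from baseline, so a T3 rater needs no programme date. The programme questionnaires are not given at T3, and the cost window often falls after DNK has ended. The expectation in Background is the authors' hypothesis, not a record of what each rater believes. All of this stands, and it is why the point is about an uncontrolled risk and not a demonstrated bias.

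The shifts of 0.10 to 0.20 SD have no source in the document, and the same table would fit any t test of this size. That also stands: the table shows sensitivity only.

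A further objection is that the article condenses a fuller ethics-committee protocol, which is not shown, and that rater assignment and questionnaire order belong there. This stands in part. If that protocol masks follow-up raters, reporting that rule settles most of the point. But the article does not merely stay silent: it states how far blinding extends, and it gives the rating team tasks that can end it.

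Finally, raters are trained, changing interviewers may cost response, and many ratings are already made. These points limit the fix but do not answer the concern.

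**Conclusion.** The point holds in a limited form. A judgement-based primary outcome is rated at follow-up by the research team with blinding stated for baseline only, with several routes by which raters could learn the arm, with no described safeguard, and with no analysis that could remove the effect. Knowledge of the arm at T3 is inferred. Size and direction are unknown, though a shift towards DNK is the plausible one given the stated expectation.

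The figures of 11% to 29% at 100 per arm (14% to 41% at 150) rest on assumed shifts of 0.10 to 0.20 SD, no true effect and a two-sided .05 test. They show that a small rating shift would matter at this sample size; they do not estimate the bias.

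The point concerns the SSM-D alone. Registered recidivism comes from judicial records and does not depend on the rater. This is an inexpensive improvement worth making, not a flaw that invalidates the trial.

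**What to change.** For the remaining T2 and T3 visits:

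1. Where the existing team allows, have the SSM-D scored by a member who did not randomise that man, did not do his programme-start or T1 assessment (nor, for T3, his T2 programme questionnaires), and has not been told his arm.
2. Score and lock the SSM-D first in the session, before any programme or cost questionnaire, and ask the man not to name his programme.
3. Have the rater record whether the arm was known and, if not, a guess.

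Report the proportion unblinded by arm. As a sensitivity check, report the SSM-D result separately for ratings made before and after the change, by calendar period. Because visits are timed from baseline, the period of a T3 visit should not depend on the arm, so each period keeps roughly the randomised comparison. The check is descriptive: with at best about 50 analysed men per arm in each period, the standard error is √(2/50) = 0.20 SD per period and √(0.20² + 0.20²) = 0.28 SD for the difference between periods, too wide to confirm or exclude a 0.20 SD shift.

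Do not base a conclusion on the subset whose arm stayed unknown, because that subset is selected after randomisation. State the ratings already made without stated masking as a limitation on the SSM-D result.

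The cost is a reallocation of visits, a fixed questionnaire order and one form item. Scheduling becomes less free, and some men lose a familiar interviewer, which may cost a little response. The article does not give the team size, so the first rule may not always be workable; the second and third do not depend on it. Some unblinding will remain, because asking about daily activity or mental health can bring the programme up.
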